### Subgroup analysis

Subgroup analyses will be performed according to sex, presence or absence of AKI, use of RRT, presence or absence of diabetes, duration of the intervention period, duration of mobilization, and baseline severity based on the APACHE II score.

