### Interventions

The intervention in this study will not involve differences in the intensity or frequency of rehabilitation; the focus will be on modifying protein intake between the two groups. In the control group, nutritional support will target the lower limit of protein intake recommended in current guidelines (1.2 g/kg/day) [9, 10]. In contrast, participants in the intervention group will receive a higher protein intake of 1.8 g/kg/day. As described previously, both caloric and protein intake will be adjusted to remain within 100–110% of the prescribed targets. Although European Society for Clinical Nutrition and Metabolism guidelines suggest higher protein targets for selected populations, such as trauma or obese patients [9], the present trial is not designed to individualize protein prescription based on diagnostic subgroups, but rather to evaluate the effect of two predefined protein targets under standardized mobilization conditions. Randomization is expected to distribute such patient characteristics evenly between groups.

The core intervention period will continue from Day 3, when protocolized protein delivery is initiated, until ICU discharge, death, or the initiation of oral intake, whichever occurs first, for a maximum of 28 days from randomization. During this period, standardized high-intensity mobilization will be provided as part of routine ICU care to all eligible patients.

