### Randomization

Written informed consent will be obtained from patients who are expected to require mechanical ventilation for > 48 h. Once consent is obtained, randomization will be performed. The consent process will be completed within 24 h of initiating mechanical ventilation.

Randomization will be conducted using a variable block method, with block sizes of four, six, or eight selected at random, and patients will then be allocated to the two groups in a 1:1 ratio. Allocation will be performed by an independent third party who is not involved in clinical care or data analysis. To ensure allocation concealment, clinical staff will be informed of the assigned group only after patient enrollment.

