### Data collection

Baseline characteristics will be collected at the start of the intervention, and will include demographic and clinical data: age, sex, body mass index, primary diagnosis, and comorbidities assessed using the Charlson Comorbidity Index [26]. Severity of illness will be measured using the Acute Physiology and Chronic Health Evaluation (APACHE) II score. Additional clinical variables will include the presence of acute kidney injury (AKI) according to the Kidney Disease: Improving Global Outcomes criteria [27], presence of diabetes, score on the Malnutrition Universal Screening Tool [28], and the presence of malnutrition defined by the Global Leadership Initiative on Malnutrition criteria [29]. Furthermore, body composition will be assessed at enrollment using a bioelectrical impedance analyzer (InBody BWA2.0S; InBody Japan, Tokyo, Japan) to determine parameters including skeletal muscle mass, skeletal muscle index, fat-free mass index, and phase angle. Baseline FIM scores will not be collected because most patients are unable to undergo functional assessment at ICU admission due to sedation, mechanical ventilation, or impaired consciousness. Therefore, FIM was assessed only at hospital discharge, consistent with the study objective of evaluating post-ICU functional recovery.

Nutritional data will include the number of days from admission to initiation of enteral nutrition, the number of days until the target protein dose was achieved, and the mean intake of caloric, protein, parenteral caloric, enteral caloric, parenteral amino acid, and enteral protein during the intervention period. These data will be analyzed separately for Days 0–1 and from Day 3 onward.

Rehabilitation-related data will include the number of days from admission to initiation of mobilization, number of days mobilization was performed, and the ICU Mobility Scale score at ICU discharge [30].

In addition, treatment-related data will include the use of renal replacement therapy, use of ECMO, and the duration of mechanical ventilation.

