This study is designed as a participant- and assessor-blinded randomized controlled trial, in which patients will remain blinded, while outcome assessors will also be blinded to group allocation to ensure reliability of the results. Another notable feature is the use of individualized caloric prescriptions based on REE measured through indirect calorimetry. This approach minimizes the risk of metabolic complications associated with overfeeding while ensuring appropriate nutritional management. Moreover, by balancing caloric targets with protein goals and employing an automated VBA-based calculation tool to determine formula and supplemental products, the study will enhance both precision and reproducibility in nutrition planning.

Several potential limitations should also be acknowledged. First, this is a single-center study, which may limit the generalizability of the findings. The single-site design was chosen for practical reasons, as relatively few ICUs are currently equipped with MPL, and its use requires specialized training. Second, the participant- and assessor-blinded design cannot completely eliminate the risk of treatment bias. To mitigate this concern, assessor blinding has been incorporated to minimize potential bias in outcome evaluation. Third, the duration of the intervention may vary among patients, with longer exposure potentially leading to greater functional improvement. To address this, ANCOVA including intervention duration as a covariate will be performed, and planned subgroup analyses will further account for potential heterogeneity.

Although recent post-hoc analyses have suggested potential harm of higher protein intake in patients with severe AKI [13], current guidelines do not recommend routine protein restriction.

Our protocol incorporates daily renal monitoring, predefined safety-driven adjustments, and planned subgroup analyses to address this concern.

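### Two of the seven subgroup factors are durations fixed only after randomisation, and a third (use of RRT) has no time window, so arms within those strata may not be comparable

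*Protocol article*

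**What the plan says.** The Subgroup analysis section names seven factors: sex, AKI, and then "use of RRT, presence or absence of diabetes, duration of the intervention period, duration of mobilization, and baseline severity" by APACHE II. The word baseline is attached only to severity, and no factor is given a time of measurement.

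The timing comes from other sections:

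- **Randomization:** "The consent process will be completed within 24 h of initiating mechanical ventilation", and "Once consent is obtained, randomization will be performed".
- **Interventions:** "The core intervention period will continue from Day 3, when protocolized protein delivery is initiated", and it runs "until ICU discharge, death, or the initiation of oral intake, whichever occurs first", capped at 28 days from randomisation.
- **Data collection:** days of mobilisation are rehabilitation data gathered over the stay. AKI, diabetes and APACHE II are in the baseline paragraph. RRT is in a separate paragraph: "treatment-related data will include the use of renal replacement therapy", listed beside ECMO and ventilation duration.
- **Outcome:** patients who die before hospital discharge receive the minimum FIM motor score, 13. ICU length of stay is a secondary outcome.
- **Discussion:** after noting that exposure will vary and that longer exposure may bring more functional gain, the authors propose an ANCOVA and add that "planned subgroup analyses will further account for potential heterogeneity".

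**The concern.** A subgroup effect is a randomised comparison when membership is settled before allocation. If membership is settled afterwards and the assigned arm can influence it, each stratum may hold different kinds of patients in the two arms.

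The plan leaves room for that influence in three places.

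1. **Duration is tied to outcomes.** The intervention period ends at death, at ICU discharge or when oral intake starts. The short-duration stratum therefore mixes early deaths, scored 13 on the primary outcome, with fast recoverers. If the arm changes mortality or speed of recovery, that mix differs between arms.
2. **Mobilisation is set by unblinded staff.** Physicians and nurses know the allocation (Blinding and masking procedures) and decide the number of sessions (Rehabilitation protocol). Mobilisation exposure could differ by arm with no biological effect of protein.
3. **Renal course is linked to dose.** The Nutrition protocol lets protein delivery be changed for renal deterioration, and the Discussion cites reported harm of higher protein in severe AKI. An effect of the arm on RRT use is therefore possible.

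The trial's hypothesis is a synergy between protein and mobilisation. A larger difference in the long-duration or high-mobilisation stratum would naturally be read as dose-response or synergy, and the Discussion invites that reading.

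**Working it through.** **Step 1. Place each factor in time against randomisation.**

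| Factor | Source | Known at randomisation? |
|---|---|---|
| Sex | Data collection, baseline | Yes |
| AKI | Data collection, baseline | Yes, if taken as AKI at enrolment |
| Diabetes | Data collection, baseline | Yes |
| APACHE II | Data collection, baseline | Yes |
| Duration of intervention period | Interventions | No: its end point always follows randomisation |
| Duration of mobilisation | Data collection, rehabilitation data | No: accrues during the ICU stay |
| Use of RRT | Data collection, treatment data | Not stated: no time window |

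Two of seven (2/7 = 29%) are certainly post-randomisation. RRT is the third doubtful one (3/7 = 43% if it is counted). Its grouping with treatment data suggests use during the stay, but the text does not fix this.

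**Step 2. Does splitting on such a factor create a difference when protein has no effect?** The documents give no figure for how far the arm might shift duration, so this step rests on assumptions. The only input from the protocol is the SD of 20 (Sample size estimation).

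Model: u is a standard normal latent severity and e is independent standard normal noise.

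- FIM = 60 − 20 × (ρ·u + √(1 − ρ²)·e), with no arm effect. The mean of 60 is arbitrary.
- Duration = u + shift × arm, with the shift in SD units of u.
- Strata: split at the overall median of duration. Two million simulated patients, allocated 1:1.

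Arm difference in mean FIM:

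| Shift | ρ | Overall | Short stratum | Long stratum |
|---|---|---|---|---|
| 0 | 0.3 | −0.05 | 0.00 | −0.09 |
| 0 | 0.5 | 0.01 | 0.00 | 0.03 |
| 0 | 0.7 | −0.04 | −0.01 | −0.05 |
| 0.25 | 0.3 | 0.00 | 0.92 | 0.99 |
| 0.25 | 0.5 | 0.02 | 1.61 | 1.62 |
| 0.25 | 0.7 | 0.02 | 2.22 | 2.28 |
| 0.5 | 0.3 | −0.05 | 1.90 | 1.83 |
| 0.5 | 0.5 | 0.00 | 3.20 | 3.17 |
| 0.5 | 0.7 | −0.02 | 4.43 | 4.43 |

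With no shift, the stratum differences are about zero. With a shift of 0.25 to 0.5 SD, both strata show a spurious difference of about 0.9 to 4.4 points in the same direction, while the overall difference stays near zero. The model does not include deaths or the score of 13, so it illustrates the mechanism and does not forecast this trial.

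**Step 3. Put that against the precision of a subgroup.** With 90 patients and even splits, each arm has about 22 per stratum. The standard error of a difference is 20 × √(1/22 + 1/22) = 6.0 points. The illustrated bias is 0.9/6.0 = 0.15 to 4.4/6.0 = 0.73 standard errors, and at most 4.4/17 = 26% of the 17-point planning difference.

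**The case against.** Several points limit the concern.

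- **The primary result is untouched.** It stays an intention-to-treat comparison of all randomised patients. Nothing in the Subgroup analysis section makes the subgroups confirmatory. This stands and limits the point to interpretation.
- **Selection common to both arms does not bias.** A reader might infer that mixing early deaths with fast recoverers is enough to make the arms non-comparable. It is not, because the mix is the same in both arms unless the arm changes duration or survival. The zero-shift rows show this. Any claim of bias must be conditional.
- **RRT is not shown to be post-randomisation.** A reader might count three such factors. The text gives no window, and RRT already running at randomisation would be a valid subgroup factor. Nor do the documents say what prompts RRT.
- **Renal harm would not vanish from the report.** A reader might infer that an RRT subgroup conceals it. Discharge creatinine and maximum blood urea nitrogen are safety outcomes, and RRT use is collected for all patients. What remains is narrower: RRT itself is not among the safety outcomes and appears only as a treatment variable, a subgroup factor and an adjustment factor.
- **The illustrated bias is small against the noise.** It is below one standard error in every row. This stands, but the bias does not average out with more data, and it would be read together with a chance finding.
- **The ANCOVA on durations is called exploratory.** Statistical analyses says so and acknowledges that durations vary despite randomisation. The subgroup section carries no such caveat, and the Discussion offers subgroups as a further answer to variable exposure.

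**Conclusion.** The point holds in a limited form. Two of seven subgroup factors are determined after randomisation, and a third can be as written. Because death both ends the intervention period and fixes the FIM motor score, the duration strata are partly defined by the outcome they are meant to explain. Comparisons within these strata are protected by randomisation only if the arm leaves the factor unchanged, and the plan gives reasons to doubt that without establishing a shift.

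The size is unknown from the documents: about zero without an arm effect on the factor, and 0.9 to 4.4 FIM points under the assumed shifts and correlations. The documents do not support saying that the strata are certainly biased or that the main conclusion is at risk. This should be corrected because the protocol has already fixed these factors and points readers towards an exposure-response reading of them.

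**What to change.** 1. Delete duration of the intervention period and duration of mobilisation from the subgroup list. Describe both by arm as process measures.
2. Limit subgroups to factors known at randomisation: sex, AKI at enrolment, diabetes, APACHE II and, if wanted, RRT already running at randomisation. State the time point for AKI and RRT.
3. Report RRT started after randomisation by arm as a safety outcome.
4. Amend the Discussion so that it no longer presents subgroup analyses as a way to account for varying intervention duration.

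Cost: two planned subgroup analyses are lost and one is redefined. RRT use is already planned for collection. Separating prior from new RRT needs its start to be dated against randomisation, which the article does not mention. The sample size and primary analysis do not change. Trial status reports that no participant had been enrolled at manuscript submission. If enrolment has since begun, the change should be dated and made before any unblinded comparison.

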## Discussion

This study is designed to evaluate whether high-protein nutrition contributes to improved physical function in critically ill patients, specifically focusing on a cohort undergoing earlier and more intensive mobilization than is typical in conventional practice. The findings are expected to provide valuable evidence on the potential synergistic effects of high-protein nutrition and rehabilitation.

Previous studies have shown that both high-protein nutrition and early mobilization, when implemented separately, offer only modest benefits. Moreover, several trials have investigated the combined use of nutrition and exercise therapy. For example, RCTs conducted by Wu et al. [32] and de Azevedo et al. [33] examined the effect of combined interventions. In the study by Wu et al. [32], a four-arm comparison was performed to assess resistance training with or without beta-hydroxy-beta-methylbutyrate (HMB) supplementation. Although the intervention improved certain aspects of physical function, the nutritional component was based on HMB rather than dietary protein intake set at a level that could be classified as high-protein nutrition.

In the study by de Azevedo et al. [33], high-protein nutrition (2.0–2.2 g/kg/day) was combined with exercise using a cycle ergometer. While the protein intake satisfied the criteria for high-protein nutrition, the simultaneous intensification of both exercise and diet made it difficult to isolate the independent contribution of each intervention. Moreover, the cycle ergometer primarily provides aerobic exercise, raising concerns regarding variability in exercise intensity and limited muscle loading.

In contrast, the present study will employ an MPL to deliver standardized, high-intensity mobilization (defined as standing or higher) for all participants, thereby ensuring consistency in exercise intensity and implementation. By using protein dose as the sole intervention variable, this study will enable a more rigorous evaluation of the direct effects of protein intake on physical function. Furthermore, MPL can be safely applied even in patients with mild consciousness disturbances or muscle weakness, enhancing both the standardization of rehabilitation and the inclusiveness of the intervention cohort.

This study is designed as a participant- and assessor-blinded randomized controlled trial, in which patients will remain blinded, while outcome assessors will also be blinded to group allocation to ensure reliability of the results. Another notable feature is the use of individualized caloric prescriptions based on REE measured through indirect calorimetry. This approach minimizes the risk of metabolic complications associated with overfeeding while ensuring appropriate nutritional management. Moreover, by balancing caloric targets with protein goals and employing an automated VBA-based calculation tool to determine formula and supplemental products, the study will enhance both precision and reproducibility in nutrition planning.

Several potential limitations should also be acknowledged. First, this is a single-center study, which may limit the generalizability of the findings. The single-site design was chosen for practical reasons, as relatively few ICUs are currently equipped with MPL, and its use requires specialized training. Second, the participant- and assessor-blinded design cannot completely eliminate the risk of treatment bias. To mitigate this concern, assessor blinding has been incorporated to minimize potential bias in outcome evaluation. Third, the duration of the intervention may vary among patients, with longer exposure potentially leading to greater functional improvement. To address this, ANCOVA including intervention duration as a covariate will be performed, and planned subgroup analyses will further account for potential heterogeneity.

Although recent post-hoc analyses have suggested potential harm of higher protein intake in patients with severe AKI [13], current guidelines do not recommend routine protein restriction.

Our protocol incorporates daily renal monitoring, predefined safety-driven adjustments, and planned subgroup analyses to address this concern.

## Trial status

Protocol version 1.0 was finalized on September 10, 2025, following approval by the institutional ethics committee. The trial was registered on September 29, 2025. Patient recruitment began on September 30, 2025, and is expected to be completed by May 31, 2027. At the time of manuscript submission, recruitment had begun, but no participants had yet been enrolled.

## Data Availability

The datasets generated and/or analyzed during the current study are not publicly available due to patient confidentiality but are available from the corresponding author on reasonable request.

## Abbreviations

AKI: Acute kidney injury
APACHE II: Acute Physiology and Chronic Health Evaluation II
BPI: Brief Pain Inventory
ECMO: Extracorporeal membrane oxygenation
FIM: Functional Independence Measure
ICU: Intensive care unit
MMSE: Mini-Mental State Examination
MPL: Mobile patient lift
REE: Resting energy expenditure
